### **3.5 Outliers**

There is a separate procedure for the data management and queries solving in the DECIDE-Salt study. All data will be cleaned and datasets be closed formally before starting the statistical analyses described in this document. Thus, no more specific procedures for outliers in main outcomes will be conducted.

## **4. Description of study population**

### **4.1 Study flow diagram**

The “CONSORT” diagram comprising the total number, number of people screened, eligible, consented, randomized, receiving their allocated intervention, withdrawing/lost to follow-up will be used for summarization.

The number of ineligible participants, if any, will be reported, with reasons for ineligibility. The reasons for lose to follow-up over the course of the trial will be classified as “death”, “hospitalization”, “temporary leave of absence”, “quit”, “else”.

The study flow chart will be represented in **Figure 1**.

### **4.2 Baseline characteristics**

Participants will be described with respect to demographic information (age, gender, race, education), anthropometrics (weight, height, BMI), physical examination (SBP, DBP, HR), life style and diet habits, labs (serum potassium, renal function, urinary electrolytes), comorbidities, medication history at baseline, both overall and separately for the intervention and control groups.

Categorical data will be summarized by numbers and percentages. Continuous data will be summarized by mean, SD and range if data are normal and median, IQR and range if data are skewed. Minimum and maximum values will also be presented for continuous data.

Baseline characteristics will be described in **Table 1**.

## **5. Analysis methods**

### **5.1 Primary outcome**

The primary outcome is SBP evaluated during 24-month follow-up, to be compared between intervention groups.

#### **5.1.1 Primary analysis**

The primary analysis will be performed in FAS dataset. The results will be regarded as the main findings.

A pre-specified linear mixed effects model will be performed to model repeated measures of SBP of the same individual over time. The model will include intervention status and baseline SBP as fixed effects, as well as cluster and time as random effects. Separated models will be built for each intervention, either SS alone or SSSC alone. The model would be:

$$y_{ijt} = \beta_0 + \mu_{1i} + \mu_{2j} + \beta_1 x_{ij} + \beta_2 c_{ij} + \beta_3 t + e_{ijt}$$

$$e_{ijt} \sim N(0, \sigma_e^2)$$

$$\mu_{1i} \sim N(0, \sigma_{\mu 1}^2)$$

$$\mu_{2j} \sim N(0, \sigma_{\mu 2}^2)$$

Where  $i$  represents the  $i^{\text{th}}$  subjects,  $j$  represents the  $j^{\text{th}}$  cluster (facility),  $t$  represents time point  $t$ ,  $y_{ijt}$  is the SBP measured for subject  $i$  in cluster  $j$  at time  $t$  (follow-up month), baseline SBP will not be included in  $y_{ijt}$ ;  $\beta_0$  is the mean outcome in the control group at baseline;  $\mu_{1i}$  is an individual random effect to allow for multiple repeats per person;  $\mu_{2j}$  is a cluster random effect on baseline SBP to allow for between-cluster heterogeneity;  $x_{ij}$ , the predictor of interest, either SS or SSSC, is an indicator of the intervention for subject  $i$  in cluster  $j$  (1 indicates receive intervention while 0 indicates not receive intervention);  $\beta_1$ , the coefficient of interest, is the effect coefficient of intervention;  $c_{ij}$  is the baseline SBP measured for subject  $i$  in cluster  $j$ ;  $e_{ijt}$  is the random error for the measurement of subject  $i$  in cluster  $j$  at time  $t$ .

The estimation of  $\beta_1$ , its 95% confidence interval and the corresponding  $p$  value will be reported in **Table 2**.

We will also evaluate the interaction between SS and SSSC in lowering SBP during study period. If the effect of both interventions do exist, we will add interaction term in the above model to test the interaction between SS and SSSC. The model would be:

$$y_{ijt} = \beta_0 + \mu_{1i} + \mu_{2j} + \beta_1 x_{1ij} + \beta_2 x_{2ij} + \beta_3 x_{1ij} * x_{2ij} + \beta_4 c_{ij} + \beta_5 t + e_{ijt}$$

$$e_{ijt} \sim N(0, \sigma_e^2)$$

$$\mu_{1i} \sim N(0, \sigma_{\mu 1}^2)$$

$$\mu_{2j} \sim N(0, \sigma_{\mu 2}^2)$$

Where  $i$  represents the  $i^{\text{th}}$  subjects,  $j$  represents the  $j^{\text{th}}$  cluster (facility),  $t$  represents time point  $t$ ,  $y_{ijt}$  is the SBP measured for subject  $i$  in cluster  $j$  at time  $t$  (follow-up month), baseline SBP will not be included in  $y_{ijt}$ ;  $\beta_0$  is the mean outcome in the control group at baseline;  $\mu_{1i}$  is an individual random effect to allow for multiple repeats per person;  $\mu_{2j}$  is a cluster random effect

on baseline SBP to allow for between-cluster heterogeneity ;  $x_{1ij}$  , one of the predictors of interest, is an indicator of the intervention SS for subject  $i$  in cluster  $j$  (1 indicates receive SS while 0 indicates not receive SS);  $\beta_1$  , the coefficient of interest , is the effect coefficient of SS;  $x_{2ij}$  , one of the predictors of interest, is an indicator of the intervention SSSC for subject  $i$  in cluster  $j$  (1 indicates receive SSSC while 0 indicates not receive SSSC);  $\beta_2$  , the coefficient of interest , is the effect coefficient of SSSC;  $\beta_3$  is the effect coefficient of SS and SSSC interaction;  $c_{ij}$  is the baseline SBP measured for subject  $i$  in cluster  $j$ ;  $e_{ijt}$  is the random error for the measurement of subject  $i$  in cluster  $j$  at time  $t$ .

The estimation of  $\beta_1$  ,  $\beta_2$  ,  $\beta_3$  and their 95% confidence interval and the corresponding  $p$  value will be reported in **Table 2**.

We will not adjust for the multiple tests, i.e. we will test both primary aims at  $p=0.05$ , because the efficacy and effectiveness of salt substitute in lowering blood pressure has been proved in previous studies with RCT design and our current study on this specific intervention is considered an implementation study, which will inform us the effectiveness of applying the particular intervention in this particular setting, senior residential facilities. Only the SSSC is considered a novel intervention that has never been rigorously tested before.

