## **2.4 Randomization**

The 48 eligible senior residential facilities (clusters) were randomized through a central computerized process in a 1:1:1:1 allocation ratio to the 4 intervention groups, with stratification by four regions, (Changzhi , Xi'an, Hohhot and Yangcheng). An independent statistician carried out the randomization after the baseline characteristics had been collected for study sites and individual participants. The allocation codes are kept by the statistician, and only the local staff responsible for the implementation of interventions have been informed. The outcome assessment team is independent of the staff responsible for implementing the interventions

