## **2.5 Sample size**

The study was designed to provide at least 80% power (with a 2-sided  $\alpha = 0.05$ ) to detect a net reduction in mean SBP of at least 3.0 mm Hg between groups with either or both interventions compared to control. The power estimate assumed a standard deviation of systolic blood pressure of 18 mmHg based on previous studies, an intra-cluster correlation coefficient of 0.02, and a loss of follow-up rate of 20%, resulting in a sample size of 960 individuals drawn from 48 clusters, each with 20 participants.

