### **3.1 Confidence intervals and p values**

All applicable statistical tests will be 2-sided and will be performed using a 5% significance level. All confidence intervals presented will be 95% and two-sided.

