### 5.3.2 Randomized comparisons

#### 5.3.2.1 Incidence of hyperkalemia

Only participants without hyperkalemia at baseline will be included in the study. A generalized linear mixed model accounting for clustering will be used for incidence of hyperkalemia

- 1) To evaluate the effect of SS or SSSC alone, the model will be:

The model will include intervention status as fixed effects, as well as cluster as random effects. Thus, the model would be:

$$\begin{aligned} \text{Logit}(P(y_{ij} = 1)) &= \beta_0 + \mu_j + \beta_1 x_{ij} + e_{ij} \\ e_{ij} &\sim N(0, \sigma_e^2) \\ \mu_j &\sim N(0, \sigma_{\mu_j}^2) \end{aligned}$$

Where  $i$  represents the  $i^{\text{th}}$  subjects,  $j$  represents the  $j^{\text{th}}$  cluster (facility),  $y_{ij}$  is the probability of hyperkalemia for subject  $i$  in cluster  $j$ ;  $\beta_0$  is the mean outcome in the control group;  $\mu_j$  is a cluster random effect to allow for between-cluster heterogeneity;  $x_{ij}$ , the predictor of interest, either SS or SSSC, is an indicator of the intervention for subject  $i$  in cluster  $j$  (1 indicates receive intervention while 0 indicates not receive intervention),  $\beta_1$ , the coefficient of interest, is the effect coefficient of intervention;  $e_{ij}$  is the random error for the measurement of subject  $i$  in cluster  $j$ .

2) To test the interaction effect of SS and SSSC, the model will be:

The model will include intervention status as fixed effects, as well as cluster as random effects. Thus, the model would be:

$$\begin{aligned} \text{Logit}(P(y_{ij} = 1)) &= \beta_0 + \mu_j + \beta_1 x_{1ij} + \beta_2 x_{2ij} + \beta_3 x_{1ij} * x_{2ij} + e_{ij} \\ e_{ij} &\sim N(0, \sigma_e^2) \\ \mu_j &\sim N(0, \sigma_{\mu_j}^2) \end{aligned}$$

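### The primary SBP models leave out the other randomised intervention and the region stratum, so standard errors are somewhat too large whenever either matters

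*Supplement*

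**What the plan says.** SAP 2.4 says the facilities were "randomized through a central computerized process in a 1:1:1:1 allocation ratio to the 4 intervention groups", "with stratification by four regions". Each main effect therefore compares 24 facilities with 24.

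SAP 5.1.1 describes the primary SBP model thus: "The model will include intervention status and baseline SBP as fixed effects, as well as cluster and time as random effects". It then says: "Separated models will be built for each intervention, either SS alone or SSSC alone". The equation has one intervention indicator, baseline SBP, a time term, and subject and facility random effects. It has no term for the other intervention and none for region.

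The two indicators appear together for SBP only under a condition: "If the effect of both interventions do exist, we will add interaction term in the above model to test the interaction between SS and SSSC".

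SAP 5.1.2.1 gives an adjusted model as a secondary analysis. It adds only baseline covariates that differ at p<0.05. Elsewhere in the SAP's analyses, region serves as a subgroup factor (5.6), as centre in the imputation model (3.4), for summaries of salt-supply compliance (5.5), and in a sensitivity analysis without Xi'an (5.7). No reason is given for leaving either term out of the primary model. SAP 5.2.1 uses the same models for the continuous secondary outcomes.

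**The concern.** The other intervention and region are both facility-level factors, and the randomisation balances both across the comparison being estimated. Leaving out such a factor does not bias the intervention coefficient. It does move variation that the design could explain into the facility random effect, and that variance sets the standard error. The true sampling variability of the estimate is unchanged, so the model reports more uncertainty than there is. Intervals are then too wide, and the test rejects less often than its nominal rate under the null and less often than it could under the alternative.

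At stake are precision and calibration, not validity. The planned analysis would give away part of what the factorial, stratified design was built to provide.

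**Working it through.** **Inputs.** Protocol V1.4, section 10: SS effect 3.0 mmHg, SSSC effect 4.0 mmHg, SD 18 mmHg, ICC 0.02, 48 facilities, 16 evaluable in each. SAP 3.1: two-sided 5%. Assumed, because the documents do not give them: within-person correlation r = 0.5 for the repeated-measures case, and a between-region SD of 0 to 3 mmHg.

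**The plan's own figures.** The protocol states 80% power for 3 mmHg and 96.6% for 4 mmHg. With 24 v 24 facilities, these inputs give 52.6% and 77.1%. The stated figures reproduce only with 48 facilities per arm (81.7% and 96.9% by a z calculation; 80.9% and 96.6% by a t calculation). That is a separate matter. Here it shows only that precision is not in surplus.

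**Variance of a facility mean.** 18² × [0.02 + 0.98 × w/16].
- Single follow-up value, w = 1: 324 × 0.08125 = 26.33. SE of the main effect = √(26.33 × 4/48) = 1.48.
- Mean of four visits adjusted for baseline, w = (1 + 3r)/4 − r² = 0.625 − 0.25 = 0.375: 324 × 0.04297 = 13.92. SE = √(13.92 × 4/48) = 1.08.

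**Leaving out the other intervention.** A balanced factor with effect d adds d²/4 to the facility variance that the model sees. For d = 4 this is 4.0, against a between-facility variance of 0.02 × 18² = 6.48. The reported SE becomes √((V + d²/4)/12), while the true sampling SD stays √(V/12). Power is Φ[(effect − 1.96 × reported SE)/true SD].

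SS model, power for 3 mmHg:

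| Average SSSC effect | Single visit: SE, inflation, power | Four visits: SE, inflation, power |
|---|---|---|
| 0 (same as joint model) | 1.48, 0%, 53% | 1.08, 0%, 80% |
| 2 mmHg | 1.51, 2%, 51% | 1.12, 4%, 78% |
| 3 mmHg | 1.54, 4%, 49% | 1.16, 8%, 75% |
| 4 mmHg | 1.59, 7%, 47% | 1.22, 13%, 71% |

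SSSC model, with a 3 mmHg SS effect left out (adds 2.25): SE 1.54 v 1.48 for a single visit, or 1.16 v 1.08 for four visits. Power for 4 mmHg is 74% v 77%, or 94% v 96%.

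**Simulation.** Runs of 48 facility means (40,000 replicates) agree. With no SS effect and a 4 mmHg SSSC effect, the separate SS model rejects in about 4.2% (single visit) or 3.0% (four visits) of runs. The joint model rejects in about 5.7% under the same z test, which is slightly liberal with 48 facilities.

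**Leaving out region as well.** The between-region variance is added on top. With a 4 mmHg SSSC effect also omitted:

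| Assumed region SD | SS SE inflation: single / four visits | SS power: single / four visits |
|---|---|---|
| 0 | 7% / 13% | 47% / 71% |
| 1 mmHg | 9% / 17% | 46% / 68% |
| 2 mmHg | 14% / 25% | 42% / 63% |
| 3 mmHg | 22% / 39% | 36% / 52% |

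The joint model with region gives about 53% and 80% throughout. With no region differences, adding region changed power by no more than simulation error.

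**The case against.** **The 4 mmHg case is the top of the range.** Protocol section 5.4 steps salt use down to targets of 20%, 30%, 40% and 40% below baseline at months 6, 12, 18 and 24, a mean of 32.5%. If the SBP effect is proportional to the reduction (an assumption), the four-visit average is 4 × 32.5/40 = 3.25 mmHg. The added variance is then 2.64, SE inflation about 5% (single visit) or 9% (four visits), and the power loss about 4 to 5 points. This stands, and is why the size is given as a range.

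**The novel comparison is hardly touched.** SAP 5.1.1 treats only SSSC as new, and its power falls by just 2 to 3 points. This also stands.

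**Region is unquantified.** No between-region variance appears in the documents. If the ICC of 0.02 already includes regional differences, the region term is better seen as precision not gained than as precision lost. This stands too.

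**The SAP does fit both factors when both work.** That is true, but with a product term in the model the SS and SSSC coefficients are simple effects, each at the absent level of the other intervention. They are not the factorial main effects. The covariates added in SAP 5.1.2.1 depend on a baseline significance screen, so they guarantee neither term.

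**Stronger readings a reader might infer.** One is that the event and safety models carry the same loss. They do use one indicator each, but the linear-model argument does not transfer directly to frailty or logistic models, and no size was worked out for them. For hyperkalemia, SAP 5.3.2.1 also gives a joint interaction model without the condition. Another is that arm-by-visit terms are needed to mend this. They address a different question, and SAP 5.7 already plans a month-24 change analysis and an SSSC analysis without month 6.

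**Conclusion.** The omission is real, and nothing else in the SAP repairs it for the primary main effects. Its direction is certain whenever the omitted factor matters: unbiased estimates, overstated standard errors and conservative tests. Its size is modest and conditional. For an average SSSC effect of 2 to 4 mmHg, the SS standard error is about 2–7% too large on single-visit variance, or 4–13% on a four-visit baseline-adjusted mean, and SS power falls by about 2 to 8 points. At a between-region SD of 2 mmHg and a 4 mmHg SSSC effect, total inflation would be about 14–25%.

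These figures rest on the protocol's ICC and SD, equal-sized facilities balanced within region, and the assumed r = 0.5 and region SDs. A reader might infer a fixed loss of ten or more points of power, or a risk of false-positive claims. The documents support neither: the loss disappears if the omitted effects are nil, and the error is on the cautious side.

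**What to change.** In SAP 5.1.1, replace the two separate models with one main-effects model for SBP. It should contain SS, SSSC, region as a four-level fixed effect, baseline SBP and time, with facility and subject random effects. Report both main effects from this model in Table 2. Test the SS-by-SSSC interaction in a separate model, so that its simple-effect coefficients do not take the place of the main effects. Use the same form for the continuous secondary outcomes that SAP 5.2.1 ties to the primary model, with their own baseline values.

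The cost is four facility-level degrees of freedom out of 48 facilities (one for the other intervention, three for region), a change of SAP wording and a few lines of code. No data collection changes. If the omitted effects turn out to be nil, almost nothing is lost.

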## **2.Trial Purpose**

### **2.1 Primary Purpose**

To compare the effects of using only salt substitutes, only the stepwise salt supply control,

and using both intervention strategies in tandem on reducing the blood pressure of the elderly in Nursing Homes against a control group.

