#### **➤ Management Target and Plan for Gradual Reduction of Cooking Salt Usage**

The main strategy behind this intervention is to control the person purchasing salt for the nursing homes, so as to gradually reduce salt usage in the kitchen in a stepwise manner. The intervention strategy consists of 4 stages. The first stage is the preparatory stage, which lasts for a month. The nursing homes will continue the amount of salt they normally use in their cooking and begin recording how much salt they use to be used as a baseline reference. The second stage consists of two steps, with every step lasting 3 months for a total of 6 months. At this stage, the salt reduction target for every step will be 10% from the nursing home's baseline salt usage. The third stage consists of four steps, with every step lasting 3 months for a total of 12 months. At this

stage, the salt reduction target for every step will be 5% from the nursing home's baseline salt usage. The fourth stage is the maintenance stage. The amount of salt used in the nursing homes should now decrease to 60% of their baseline salt usage. This will not be lowered further until the end of the research. (As per diagram below)

[figure not shown]

➤ Management of Stepwise Salt Supply Control and evaluation

Nursing homes that have been assigned to the SSSC group will send their purchasers and cooks to receive standardized technical training. See Annex 2 (Stepwise Salt Supply Control Technical Training) for detailed contents of the training.

Through the training, purchasers will learn and understand the salt reduction targets throughout the various stages and the specific ways to control salt supply; and cooks will learn how to weigh 5% and 10% of their ordinary salt usage. The two parties have to learn the reason for salt reduction and techniques to communicate with the elderly.

The person-in-charge from the sub-sites will audit the stock in and stock out records once every three months to evaluate if the goal for the stage has been met. This will be the basis for the

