## 9. Statistical Analysis

### **Baseline Data Analysis:**

Participants will be described with respect to demographic information (age, gender, ethnic group, education, etc.), anthropometrics (weight, height, BMI, etc.), physical examination (SBP, DBP, etc.), life style and diet habits, labs (serum potassium, renal function, urinary sodium, urinary potassium, urinary microalbumin, etc.), comorbidities, medication history at baseline, both overall and separately for the intervention and control groups. Categorical data will be summarized by numbers and percentages. Continuous data will be summarized by mean, SD and range if data are normal and median, IQR and range if data are skewed. We will conduct one-way ANOVA on continuous variables and  $\chi^2$  test on categorical variables to check if the baseline characteristics balanced across randomized groups and to identify potential confounding variables.

**Effect Evaluation:** Results from ITT analysis will be reported as the primary result and the one from PP analysis will be reported as the secondary result.

Primary outcome is the change in SBP from baseline to follow-up

Secondary outcome includes change in DBP from baseline to follow-up, changes in 24-hr urinary sodium and urinary microalbumin; the risk of developing cardiovascular events

We will use multilevel mixed-effects model to control the cluster effect and confounding variables. We will compare the difference of changes in blood pressure before and after the intervention between SS and non-SS, SSSC and non-SSSC, SS + SSSC and SS only or SSSC only respectively.

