### **1.2 Objectives**

The primary aim of the present study is to determine the efficacy of two practical and scalable sodium reduction intervention strategies on systolic blood pressure (SBP) among older adults living in senior residential facilities: (1) a stepwise reduction in the supply of regular salt to institutional kitchens and (2) replacing regular salt with salt substitute. The null hypothesis is that neither of the two sodium reduction interventions will reduce SBP. And if the effect of both interventions do exist, the interaction between SS and SSSC in lowering SBP during study period will be further analyzed.

The secondary aims are to:

- 1) evaluate the safety of these strategies, particularly risks of hyperkalemia with salt substitute and hyponatremia in those receiving either or both interventions.
- 2) evaluate whether sodium reduction intervention can reduce the risk of cardiovascular events and death
- 3) assess the cost-effectiveness and adherence of sodium reduction strategies
- 4) assess the impact of sodium reduction intervention on microalbuminuria

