#### 5.1.2.1 Controlling for potential confounders

We will test if there is any imbalance between groups in baseline variables. We will additionally include the covariates that differs significantly at the baseline ( $p<0.05$ ) to adjust confounding.

The models would be:

$$y_{ijt} = \beta_0 + \mu_{1i} + \mu_{2j} + \beta_1 x_{ij} + \beta_2 c_{ij} + \sum BZ_{ij} + \beta_3 t + e_{ijt}$$

$$e_{ijt} \sim N(0, \sigma_e^2)$$

$$\mu_{1i} \sim N(0, \sigma_{\mu 1}^2)$$

$$\mu_{2j} \sim N(0, \sigma_{\mu 2}^2)$$

Where  $i$  represents the  $i^{\text{th}}$  subjects,  $j$  represents the  $j^{\text{th}}$  cluster (facility),  $t$  represents time point  $t$ ,  $y_{ijt}$  is the SBP measured for subject  $i$  in cluster  $j$  at time  $t$  (follow-up month), baseline SBP will not be included in  $y_{ijt}$ ;  $\beta_0$  is the mean outcome in the control group at baseline;  $\mu_{1i}$  is an individual random effect to allow for multiple repeats per person;  $\mu_{2j}$  is a cluster random effect on individual baseline SBP to allow for between-cluster heterogeneity;  $x_{ij}$ , the predictor of interest, either SS or SSSC, is an indicator of the intervention for subject  $i$  in cluster  $j$  (1 indicates receive intervention while 0 indicates not receive intervention);  $\beta_1$ , the coefficient of interest, is the effect coefficient of intervention;  $c_{ij}$  is the baseline SBP measured for subject  $i$  in cluster  $j$ ;  $Z_{ij}$  is the baseline covariate other than SBP measured for subject  $i$  in cluster  $j$ ;  $e_{ijt}$  is the random error for the measurement of subject  $i$  in cluster  $j$  at time  $t$ .

If the interaction effect in primary analysis exists, then below model will be built for adjustment of covariates:

$$y_{ijt} = \beta_0 + \mu_{1i} + \mu_{2j} + \beta_1 x_{1ij} + \beta_2 x_{2ij} + \beta_3 x_{1ij} * x_{2ij} + \beta_4 c_{ij} + \sum BZ_{ij} + \beta_5 t + e_{ijt}$$

$$e_{ijt} \sim N(0, \sigma_e^2)$$

$$\mu_{1i} \sim N(0, \sigma_{\mu 1}^2)$$

$$\mu_{2j} \sim N(0, \sigma_{\mu 2}^2)$$

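### The SS-by-SSSC interaction on SBP is tested only if both main effects are found, so the combination named in the protocol's primary purpose may get no modelled estimate

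*Supplement*

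**What the plan says.** The condition appears twice in the SAP. Section 1.2 states that "if the effect of both interventions do exist, the interaction between SS and SSSC in lowering SBP during study period will be further analyzed", and section 5.1.1 repeats it as "If the effect of both interventions do exist, we will add interaction term in the above model". Neither gives a criterion; the nearest rule is the general one in section 3.1: "All applicable statistical tests will be 2-sided and will be performed using a 5% significance level".

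The headline analysis has one factor per model: "Separated models will be built for each intervention, either SS alone or SSSC alone". A second condition follows in section 5.1.2.1: "If the interaction effect in primary analysis exists, then below model will be built for adjustment of covariates".

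Other places set no such condition:

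- Protocol V1.4, section 2.1, names as primary the effects of each strategy alone "and using both intervention strategies in tandem on reducing the blood pressure of the elderly in Nursing Homes against a control group".
- Protocol V1.4, section 9, plans comparisons of blood pressure change that include "SS + SSSC and SS only or SSSC only respectively". The SAP does not carry these contrasts, and its list of revisions (section 5.9) does not record them as dropped.
- The shells of SAP Tables 2 and 3 have an interaction p-value column with no condition attached.
- SAP Figure 2 plots four-group mean SBP with 95% CIs at each visit.
- The hyperkalemia interaction model in SAP 5.3.2.1 is unconditional.

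**The concern.** A marginal effect in a 2×2 design averages the effect of one factor over the two levels of the other. It describes each strategy used alone only if the interaction is small, so the interaction estimate is needed most when a margin is weaker than expected. The SAP looks at it only when both margins are found.

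The condition also works in one direction. If the strategies overlap, both margins shrink and the test becomes less likely; if they reinforce each other, it becomes more likely. Some overlap is plausible, because under SSSC there is less kitchen salt for the substitute to replace. The protocol's end-state target reads: "The amount of salt used in the nursing homes should now decrease to 60% of their baseline salt usage".

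At stake is whether facilities should adopt one strategy or both. The protocol treats this as primary, yet the SAP may yield no modelled answer to it.

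**Working it through.** **Inputs.** Protocol section 10: SS effect 3.0 mmHg, SSSC effect 4.0 mmHg, SD 18 mmHg, ICC 0.02, 48 homes, 16 evaluable residents per home. SAP 2.4: allocation 1:1:1:1, so 12 homes per cell and 24 v 24 per factor. SAP 3.1: two-sided 5%. Assumed here: an effect exists when p<0.05 in its own model, and the sizes of interaction, since the documents give none.

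**The plan's own powers.** The design effect is 1 + 15 × 0.02 = 1.30. With 48 homes on each side, the SE is 18 × √(2 × 1.30 / (48 × 16)) = 1.05 mmHg. Power by a t test is then 80.9% at 3 mmHg and 96.6% at 4 mmHg, matching the stated 80% and 96.6%. With the 24 v 24 homes of this design, the SE is 1.48 mmHg and the powers are 50.9% and 75.3%. The stated figures are therefore reproduced only with 48 homes per side. That is a separate matter, but it lowers the chance that both effects are found.

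**Variance of a home mean.** Between homes: 0.02 × 324 = 6.48. Within homes: 0.98 × 324 / 16 = 19.84.

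- Single visit: V = 6.48 + 19.84 = 26.3.
- Mean of four visits adjusted for baseline, assumed correlation 0.5: within-home factor (1 + 3 × 0.5)/4 − 0.5² = 0.375, so V = 6.48 + 7.44 = 13.9.

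**Standard errors** (12 homes per cell):

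| Contrast | Formula | Single visit | Four visits |
|---|---|---|---|
| Marginal effect | √(V/12) | 1.48 | 1.08 |
| Simple effect v control | √(V/6) | 2.09 | 1.52 |
| Interaction | √(V/3) | 2.96 | 2.15 |

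A simple effect has twice the variance of a margin, and the interaction has twice its SE.

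**Size of antagonism.** With antagonism d, each margin equals the effect alone minus d/2. On the protocol's stepwise schedule, target salt use at months 6, 12, 18 and 24 is about 80%, 70%, 60% and 60% of baseline, a mean of 67.5%. If the SS effect scales with the salt left, d = 3.0 × 0.325 ≈ 1.0 mmHg over all visits, or 3.0 × 0.40 = 1.2 mmHg at the end-state target. At d = 3, the combination does no better than SSSC alone (3 + 4 − 3 = 4 mmHg).

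**Chance that the condition is met.** Simulated home means were tested in one-factor models, as in the SAP:

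| Interaction (mmHg) | Margins SS / SSSC | Single visit | Four visits |
|---|---|---|---|
| Synergy 3 | 4.5 / 5.5 | 70% | 94% |
| None | 3.0 / 4.0 | 31% | 64% |
| Antagonism 1.0 | 2.5 / 3.5 | 19% | 45% |
| Antagonism 1.2 | 2.4 / 3.4 | 17% | 41% |
| Antagonism 3 | 1.5 / 2.5 | 5% | 12% |

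Even on the protocol's stated powers with no interaction, 0.80 × 0.966 = 77%, so the interaction would be skipped in 23% of trials.

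**The case against.** The strongest defence is that the SAP sets two marginal primary aims, that the interaction is supportive and unpowered, and that testing it only when both strategies work is a reasonable economy. The lack of power is real: at an antagonism of 1.2 mmHg, an unconditional test has only about 7% to 8% power, so removing the condition would seldom demonstrate antagonism. But the protocol places the combination in its primary purpose, and the remedy sought is an estimate with its interval.

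A reader might also infer more than the documents support:

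- **That the headline estimand switches on a p value.** SAP 5.1.1 reports the separate-model estimates without condition and treats them as the main result; the interaction model is an addition. What remains is an ambiguity: its β1 and β2, now simple effects against control, are also sent to Table 2, and the shell does not say whether they share cells with the margins.
- **That the combination is absent from the plan.** The protocol contrasts, the Table 2 column and Figure 2 all touch it. The documents conflict, and Figure 2 is descriptive only.
- **That antagonism explains most skipped tests.** With no interaction at all, the test is skipped in 36% to 69% of trials. An antagonism of 1.0 to 1.2 mmHg adds roughly 12 to 23 percentage points.
- **That SSSC cuts kitchen salt by 40% throughout follow-up.** That is a target reached in steps, while the SAP outcome uses all visits.
- **That modest overlap would produce a null SS margin.** It would move from 3.0 to about 2.4 or 2.5 mmHg, which is weaker but not null.

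**Conclusion.** The point holds for SBP efficacy. The interaction test rests on an undefined condition, the adjusted interaction model rests on a second one, and when the first fails the SAP fits no SBP model containing both factors. This is at odds with protocol sections 2.1 and 9 and with the SAP's own table shells.

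The direction of the selection follows from the algebra of the design and needs no assumed figure. The percentages do need assumptions: p<0.05 as the criterion, the protocol's effect sizes, and the assumed interaction sizes and visit correlation. If baseline adjustment also reduced between-home variance by the factor 0.375, the condition would be met more often, in about 58% of trials at 1.2 mmHg. The conclusion would stand. The safety interaction is not affected.

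**What to change.** In SAP 1.2, 5.1.1 and 5.1.2.1, remove both conditions. Then:

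1. Always fit the SBP interaction model, unadjusted and adjusted, and report the interaction with its 95% CI.
2. Always tabulate the adjusted means of the four cells and five contrasts: SS only, SSSC only and both against control, and both against each alone.
3. State that the marginal main effects are the fixed Table 2 headline, and put the simple effects in a separate table.
4. State that the interaction SE is twice the main-effect SE, about 2.2 to 3.0 mmHg (95% CI half-width about 1.96 × 2.15 = 4.2 to 1.96 × 2.96 = 5.8 mmHg), so a non-significant interaction is not evidence of additivity.
5. Reconcile the SAP with the protocol section 9 contrasts, recording any intended departure in SAP 5.9.

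The cost is SAP wording and one table, with no new data. The small downside is that the added estimates will have wide intervals.
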